**Primary outcome measures related to walking ability**						
Performance Oriented Mobility Assessment (POMA)			x	x	x	x
10 Meter Walking Test with obstacles (10MWT_obstacle_)				x	x	
10 Meter Walking Test with cognitive task (10MWT_cognitive_)				x	x	
Trail Making Test (TMT)			x	x	x	x
Functional Ambulation Category (FAC)		x	x	x	x	x
Elderly Mobility Scale (EMS)			x	x	x	x
10 Meter Walking Test (10MWT)				x	x	
Timed Up-and-Go test (TUG)				x	x	
Nottingham Extended Activities of Daily Living (NEADL)			x		x	x
**Secondary outcome measure, related to fear of falling**						
Falls Efficacy Scale International (FES-I)			x	x	x	x
**Secondary outcome measure, related to fall incidence**						
Monthly fall diary						x
**Secondary outcome measures, related to general health**						
Visual Analogue Scale of perceived general health (VAS)			x	x	x	x
Mini-Mental State Examination (MMSE)		x				
Hip Disability and Osteoarthritis Score (HOOS)					x	x

#### T0 (pre-intervention assessments)

Outcome measures related to walking ability obtained during T0 will comprise scores of mobility (POMA [38-40], Elderly Mobility Scale EMS; [41,42]), executive function (Trail Making Test TMT; [43-45], requiring visual scanning, task shifting, planning and mental flexibility), general functional walking ability (Functional Ambulation Category FAC; [34,35]), and pre-admission activity of daily living status (Nottingham Extended Activities of Daily Living scale NEADL; [46-48]). Outcome measures related to fear of falling and general health will include perceived fear of falling (Falls Efficacy Scale International FES-I; [49,50]) and perceived general health status (visual analogue scale VAS; [51]). Demographics, medical information regarding hip fracture, co-morbidities, medication use and pre-admission daily functioning, including the use of assistive devices, will be obtained from medical files.

#### T1 (post-intervention assessments)

Similar to T0, POMA, EMS, TMT, FAC, FES-I and VAS scores of perceived general health will be obtained at T1 as well. Current living situation and the use of assistive devices will also be scored. To evaluate walking ability, we will further perform the Timed Up-and-Go test (TUG, [52]) and the 10 Meter Walk Test (10MWT, [48]). In addition to the standard 10MWT, we will also perform the 10MWT with 3 obstacles in the walkway to evaluate obstacle avoidance during walking (10MWT_obstacle_; one 10 × 20 × 5 cm and two 5 × 20 × 10 cm obstacles [height × width × length]) and while subtracting 3’s from a random number between 191 and 199 to evaluate the dual-task costs of walking (10MWT_cognitive_; the serial-3 subtraction task will first be practiced for 60 seconds). Accordingly, the serial-3 subtraction task will also be performed as a single task. The modified 10MWTs are deemed informative given the older adults’ impaired ability to avoid obstacles and their elevated attentional demands of walking – both factors related to fall risk [17,24,53-55]. The TUG and 10MWTs will be performed twice, taking the average time in seconds that is necessary to complete each test as the outcome measure. The number of serial-3 subtractions as well as the number of mistakes made will be used as additional outcome measures for evaluating the dual-task costs of walking.

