## Discussion

Falls are a common mishap among older adults and impose a major burden on older adults and the community at large; it is therefore important to gather evidence on the effectiveness of intervention programs and their design features (e.g., adaptive versus repetitive stepping, high versus low practice intensity). The current study was conceived to examine the efficacy of gait adaptability exercises in intervention programs aimed at improving walking ability and reducing fall incidence. Recently, encouraging first steps in this direction have been taken (e.g., [24,27,62,63]). Weerdesteyn et al. [24], for example, integrated overground gait adaptability exercises in a 5-week Nijmegen Falls Prevention Program for older adults, and found improved obstacle avoidance success rates, improved balance confidence and reduced fall incidence during one year follow-up. Given that the Nijmegen Falls Prevention Program consisted of overground walking, and hence practice intensity was presumably fairly low (i.e., number of steps taken per session), the observed beneficial effects are encouraging as they may be enhanced even further by increasing the practice intensity of gait adaptability exercises, such as with our C-Mill based gait adaptability training protocol.

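### The obstacle version of the 10-metre walk is meant to evaluate obstacle avoidance, but its only stated outcome is completion time, which does not register whether an obstacle was cleared or struck

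*Protocol article*

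**What the plan says.** In the protocol article, under T1 (post-intervention assessments), the obstacle walk is introduced with its purpose: "we will also perform the 10MWT with 3 obstacles in the walkway to evaluate obstacle avoidance during walking". The reason given for both modified walks begins: "The modified 10MWTs are deemed informative given the older adults’ impaired ability to avoid obstacles".

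The same paragraph then fixes the score for the TUG and every version of the 10-metre walk: each is done twice, "taking the average time in seconds that is necessary to complete each test as the outcome measure".

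The next sentence adds outcomes other than time, for the cognitive version only: "The number of serial-3 subtractions as well as the number of mistakes made will be used as additional outcome measures for evaluating the dual-task costs". No section scores obstacle contacts, gives a time penalty, or says what happens to a walk in which an obstacle is struck. The T2 section repeats the T1 tests, and Data analyses lists 10MWT_obstacle among the longitudinal outcomes without another scoring.

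Table 1 places the test among nine measures under the primary walking-ability heading, assessed at T1 and T2. It is the only listed performance test with obstacles.

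**The concern.** The score fits the stated purpose badly. Negotiating an obstacle has a speed component and an accuracy component, and only speed is scored.

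This bears most on the comparison of AT with CT. The Background section predicts that AT will be superior on the gait-adaptability aspects of walking. The Intervention program section has AT practise foot placement and obstacle avoidance, while CT moves, once gait is safe, towards walking faster and longer. If AT teaches some participants to take more care at an obstacle, a time-only score could record that as no benefit, or as a worse result.

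The Discussion section cites an earlier overground adaptability programme that "found improved obstacle avoidance success rates". A success rate is what the planned score does not supply.

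**Working it through.** **1. Purpose against score.**

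| Test | Stated purpose | Stated outcome(s) |
|---|---|---|
| 10MWT_cognitive | Dual-task cost of walking | Mean time of two walks, plus number of subtractions and of mistakes |
| 10MWT_obstacle | Obstacle avoidance | Mean time of two walks |

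For the cognitive walk, performance on the added task is scored beside time. For the obstacle walk, performance on the added task (clearing the obstacles) is not.

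**2. How the ordering can reverse.** The documents give no walking times, so these are assumed: a 20 s walk with no slowing, and *s* extra seconds for each obstacle cleared with care.

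Time when all three are cleared = 20 + 3*s*. Time when all three are struck without slowing = 20.

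- *s* = 0: 20 s against 20 s
- *s* = 1: 23 s against 20 s
- *s* = 2: 26 s against 20 s
- *s* = 3: 29 s against 20 s

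Whenever *s* is above 0, the poorer avoider gets the better score. At *s* = 0 the two cannot be told apart.

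**3. The plan's own sample size.** Inputs from Sample size: difference 3.5 POMA points, SD 4.8, correlation 0.7, two-sided alpha 0.017, power 80%. The number of follow-up measurements T is not stated; T = 3 (T1, T2, T3) is assumed.

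n = 2 (z₁₋α/₂ + z_power)² SD² [1 + (T − 1)ρ] / (T δ²)

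= 2 × (2.387 + 0.842)² × 4.8² × (1 + 2 × 0.7) / (3 × 3.5²) = 31.4, rounded up to 32 per group, as stated.

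T = 2 gives 34 and T = 4 gives 31. With 126 / 3 = 42 per group, the permitted loss is 1 − 32/42 = 23.8%, which matches the stated 24%. None of this depends on how the obstacle walk is scored.

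**4. What a contact count could show.** Each visit gives 3 obstacles × 2 walks = 6 crossings per participant, or 6 × 42 = 252 per group at T1. Allowing for clustering within a person, the effective number is 252 / (1 + 5 × ICC): 168, 101 and 72 for ICC 0.1, 0.3 and 0.5.

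Power for two proportions (normal approximation, unpooled variance) = Φ(|p₁ − p₂| / √{[p₁(1 − p₁) + p₂(1 − p₂)]/n} − z₁₋α/₂). All success rates and ICCs are assumptions. At ICC 0.3:

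| Assumed success | Power at 0.05 | Power at 0.017 |
|---|---|---|
| 75% vs 90% | 82% | 68% |
| 85% vs 95% | 67% | 51% |
| 80% vs 90% | 52% | 35% |
| 90% vs 95% | 27% | 15% |
| 95% vs 98% | 21% | 11% |

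For 75% vs 90%, ICC 0.1 to 0.5 gives 96% to 68% at 0.05, and 90% to 51% at 0.017. The count may be informative or nearly uninformative, depending on how close success is to its ceiling. The documents do not say which.

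**The case against.** **Time is not blind to avoidance.** This stands. Time over a walkway with obstacles includes the slowing needed to negotiate them, and the plain 10-metre walk at the same visits allows the added cost to be separated from general walking speed. A reader might infer that the test cannot register avoidance at all. That goes too far: what is missing is success or failure at each obstacle.

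**The test is not singled out.** This also stands. A reader might take it for the trial's key adaptability measure, but it is one of nine, the sample size uses the POMA, and the Discussion section also looks for an AT advantage on the Trail Making Test.

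**The direction of bias is not shown.** A reader might infer that timing favours CT. The documents support only a possibility. Both treadmill groups walk at comfortable speed, AT practises speeding up and slowing down from week 4, and CT starts with quality and safety. Skilled negotiation could shorten AT times.

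**The earlier programme may also have measured time.** The article mentions its success rates and says nothing on whether time was recorded, so no contrast can be drawn.

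**The parallel with the cognitive walk is loose.** The mistakes there are subtraction errors, not gait errors. The parallel holds only in that performance on the added task is scored.

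**There is partial cover elsewhere.** Trips, slips and falls are recorded monthly from T1 to T3, and the Limitations section urges care with tests that have no T0 value. Neither supplies avoidance success on this test.

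**It could be left to the analysis plan.** This does not answer the point. The article positively defines the outcome as time, and a contact not recorded at the visit cannot be recovered in analysis.

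**Conclusion.** The point holds in a limited form. As written, a struck obstacle does not count against the participant in the one listed performance test with obstacles, although the test is there to assess avoidance. A speed-accuracy trade-off could hide or reverse a true AT versus CT difference in avoidance success. That it would do so is not shown.

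No size can be attached to the effect, because the documents give neither contact rates nor the variability of the timed walk. The 20 s against 23 to 29 s example shows the mechanism on assumed times and is not an estimate. The power figures for a contact count rest wholly on assumed success rates and ICCs, so no gain in power can be claimed. Sample size and alpha are unaffected. This is a cheap improvement to a score that fits its purpose badly, not an error in the trial's calculations.

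**What to change.** - At T1 and T2, have the blinded assessor record for each obstacle walk how many of the three obstacles were touched, stepped on or bypassed.
- Report the count (0 to 6 per visit) by group beside the time, using a binomial multilevel model, and label it a supportive outcome so that it adds no primary test.
- Draw no conclusion on avoidance success from completion time alone.

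The cost is one field on the T1 and T2 form, one further model and one more reported measure. The assessor already conducts the walk, so no extra staff or procedure is needed. The downside is that the count may have little power if nearly all obstacles are cleared. It would still show whether a shorter time came with more contacts.

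### The cognitive score of the dual-task walk is a raw count over a walk of fixed distance but variable duration, so subtractions and mistakes are both confounded with walking time

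*Protocol article*

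**What the plan says.** All the relevant text is in the protocol article, Outcome measures, T1; T2 repeats the same tests.

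- **Task.** One version of the 10-metre walk is done "while subtracting 3’s from a random number between 191 and 199 to evaluate the dual-task costs of walking".
- **Time outcome.** Each timed test is done two times, "taking the average time in seconds that is necessary to complete each test as the outcome measure". Distance is therefore constant, the duration differs between people, and the duration is the main score of the test.
- **Cognitive outcome.** "The number of serial-3 subtractions as well as the number of mistakes made will be used as additional outcome measures"; their stated purpose is to assess dual-task cost. Both quantities are plain numbers. No rate, percentage or fixed time window is given here or elsewhere in the article.
- **Single-task reference.** "Accordingly, the serial-3 subtraction task will also be performed as a single task". Its duration is not stated. The only duration given concerns practice: "the serial-3 subtraction task will first be practiced for 60 seconds".

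Three other places bear on the point. The Background hypothesises better walking ability in both treadmill groups than in usual care. The Intervention program section says that conventional treadmill training moves towards faster and longer walking. The Limitations section confirms that the cognitive version of the walk is not done at T0.

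**The concern.** The time available for subtracting is the time taken to walk 10 m. The expected count is therefore the participant's subtraction rate multiplied by walking time, and the same holds for mistakes. A motor effect enters the cognitive score even when cognition has not changed.

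If training shortens the walk, as hypothesised against usual care, a treadmill arm will show fewer subtractions and fewer mistakes than usual care at identical cognitive performance. Read at face value, the first looks like a cost of training and the second like a benefit. Neither measures what happens to cognition during walking, which is the stated purpose. There is no T0 value that could expose the artefact or adjust for it.

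The single-task reference does not rescue raw counts. They can be compared across the two conditions only if the durations match.

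**Working it through.** **Plan's own figure.** There is none on this point. The sample size rests on the POMA and does not involve these counts.

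**Inputs from the protocol.** Distance 10 m; 126 participants in three equal groups, so 126 / 3 = 42 per arm; multiplicity-corrected alpha 0.017 (Sample size section).

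**Inputs assumed.** The protocol gives no walking speeds, times or subtraction rates. Those below are illustrations, varied where they matter.

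**Formulas.** Walking time t = 10 / speed. Expected subtractions = r × t, with r the rate per second. Expected mistakes = r × e × t, with e the share of responses that are errors. Scored as a rate, (r × t) / t = r, which does not depend on t. The error proportion, (r × e × t) / (r × t) = e, does not either.

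**Same cognition, different walking time** (r = 0.4 per second in both arms):

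| Assumed times | Counts | Difference in count |
|---|---|---|
| 16 s v 20 s | 6.4 v 8.0 | 1.6 / 8.0 = 20% lower |
| 18 s v 20 s | 7.2 v 8.0 | 0.8 / 8.0 = 10% lower |
| 19 s v 20 s | 7.6 v 8.0 | 0.4 / 8.0 = 5% lower |

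The relative difference equals the relative difference in time, whatever r is.

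**Mistakes.** With r = 0.3 and e = 10%, a 20 s walk (0.5 m/s) gives 0.60 expected mistakes and a 12.5 s walk (0.8 m/s) gives 0.375. Accuracy is the same, yet the faster walker appears to improve.

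**Sign reversal.** At 0.5 m/s and 0.30 per second, the count is 0.30 × 20 = 6.0. At 0.8 m/s and 0.36 per second, a 20% better rate, it is 0.36 × 12.5 = 4.5. The better performer scores lower.

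**Single-task reference.** If the single task lasts D seconds and the true rate is unchanged, the ratio of dual-task to single-task counts is t / D. With D = 20 s, a 20 s walker has ratio 1.0 and a 16 s walker 0.8, although neither has any cognitive cost. One common D matches only those whose walk happens to last that long.

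**Chance of a false between-arm difference.** Simulation with Poisson counts, mean rate 0.4 per second in both arms, log-normal rate (log-SD 0.3 to 0.5) and log-normal time (log-SD 0.3), 42 per arm, 3,000 runs, two-sample t-test:

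| Assumed times | Counts, alpha 0.05 | Counts, alpha 0.017 |
|---|---|---|
| 16 s v 20 s | about 28-43% | about 14-27% |
| 18 s v 20 s | about 10-14% | about 4-6% |
| 19 s v 20 s | about 6-7% | about 2% |

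With rates instead of counts at 16 s versus 20 s, the test is significant in about 4-5% of runs at 0.05 and 1.5% at 0.017, close to nominal.

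**The case against.** The strongest reply is that the section lists raw data and a purpose. Walking time and a single-task reference are both collected, and a condensed article may leave their combination to a fuller document. The counts do not appear as separate lines in Table 1 or in the list of modelled outcomes under Data analyses, and no t-test is specified for them. This limits the weight of the point but does not remove it. The text goes beyond listing data: it says that the numbers themselves will be used as outcome measures, and followed as written that rule misleads.

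Four stronger readings are tempting and are not supported:

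- *The single-task count is taken over a different duration.* The protocol gives no duration; the 60 seconds is for practice. Only the conditional statement holds.
- *The artefact hits an outcome on which adaptability training is predicted to win.* The superiority hypothesis concerns gait adaptability aspects of walking and does not name dual-task cost. The executive-function benefit suggested in the Discussion is to be quantified with the Trail Making Test.
- *The artefact works consistently against treadmill training.* The two counts move in opposite evaluative directions. The illustration also separates treadmill arms from usual care. It shows nothing for adaptability versus conventional treadmill training unless their walking times differ.
- *The false-positive rate is 28-43%.* That is one assumed contrast at alpha 0.05, with a test the protocol does not specify. With a small difference in time the excess nearly vanishes.

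The Limitations section does urge caution about tests without a T0 value, including this one. Its reason is possible baseline imbalance, which is a different problem.

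**Conclusion.** The point holds as a flaw in a stated scoring rule. A raw count over a fixed distance mixes cognitive performance with walking time, and walking time is expected to differ between the treadmill arms and usual care. At equal rate and accuracy, both counts fall by the same percentage as walking time: 10% for 18 s against 20 s, 20% for 16 s against 20 s. The direction follows from the definition, given similar rates and accuracy across arms. The size rests entirely on assumed times and rates, and the false-positive figures also on the assumed spread and test.

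The consequence is limited to the interpretation of dual-task cost. These are additional measures, and the sample size and the time-based walking outcomes are untouched. The wording should be changed because the correction is so cheap, but the point does not threaten the trial's main conclusions.

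**What to change.** 1. Define the cognitive outcomes as correct responses per second and the proportion of responses that are errors, in both the single-task and the dual-task condition.
2. State and record the duration of the single-task subtraction.
3. Define cognitive dual-task cost as (dual-task rate − single-task rate) / single-task rate.
4. Report it beside the motor cost, that is, the cognitive-version walking time against the plain 10-metre walking time at the same visit, so that a trade-off between walking and subtracting is visible.

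Raw counts may still be tabulated descriptively with the walking time next to them.

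Cost: a few lines of analysis wording, one extra recorded duration and slightly more analysis work. Walking time is already measured on the same test. The drawback is that rates from short walks are noisy, since each rests on only a handful of responses (6.4 expected in 16 s at 0.4 per second).

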#### T2 (retention assessments)

All tests performed at T1 will be repeated 4 weeks later at T2. In addition, the NEADL will be conducted to assess the activities of daily living performed between T1 and T2. The Hip Disability and Osteoarthritis Score (HOOS, [56,57]) will be administered to monitor symptoms and functional limitations related to the hip. In addition, participants will be asked about the use of assistive devices, tolerated walking distance, complications and physical therapy in the past four weeks. If applicable, the content of physical therapy will be recorded.

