This study protocol is designed to examine the efficacy of C-Mill gait adaptability training for improving walking ability and reducing fall incidence and fear of falling in older adults residing in inpatient rehabilitation care to recover from a fall-related hip fracture, a group particularly prone to falling [6-9]. The efficacy of C-Mill gait adaptability training will not only be contrasted against usual care, comprising of exercises in strength, balance, overground walking, transfers and activities of daily living, but also against intensity matched conventional treadmill training (i.e., without visual context presented on the belt), promoting repetitive stepping. Literature on conventional treadmill training in older adults recovering from hip injury is quite scarce, but generally positive with regard to its efficacy [32,33]. Conventional treadmill training outperforms overground gait training in that regard, most likely because of the enhanced intensity of training (i.e., defined in number of steps taken per training session). Older adults with a total hip arthroplasty, for example, performed 1000-1500 steps during a conventional treadmill training session compared to 100-150 steps during an overground gait training session of similar duration [32]. We therefore hypothesize that both conventional treadmill training and C-Mill gait adaptability treadmill training result in better outcomes related to walking ability than usual care due to the enhanced training intensity, with superior effects for C-Mill gait adaptability treadmill training on gait adaptability aspects of walking given the concurrent focus on practicing gait adaptability. The present study will thus shed light on the relative importance of high versus low practice intensity and adaptive versus repetitive stepping as key ingredients for effective intervention programs aimed at improving walking ability and reducing fall risk and fear of falling in older adults recovering from a fall-related hip fracture.

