### Intervention program

The intervention programs will be dose-matched in terms of duration (i.e., 40 minutes per session) and frequency (i.e., five sessions per week) of therapy over a 6-week inpatient intervention period. All intervention programs will be provided by physical therapists of Solis Zorggroep, Deventer, The Netherlands. Therapy sessions will typically be conducted by a single physical therapist with two participants per session; the two participants alternately exercise and rest, resulting in 20 minutes of practice per session. Physical therapists and participants cannot be blinded to group allocation.

In the *usual care* (UC) control group, participants will receive conventional physical therapy in all 30 sessions, consisting of exercises of upper-leg strength, balance, transfers, overground walking, and activities of daily living, following locally implemented guidelines of Solis Zorggroep, Deventer, The Netherlands and Deventer Hospital, Deventer, The Netherlands regarding the treatment of hip fractures.

In the *conventional treadmill* (CT) intervention group, participants will receive 15 conventional physical therapy sessions (as in UC) and 15 conventional treadmill training sessions (week 1-3: 2 per week, week 4-6: 3 per week) with an emphasis on repetitive stepping. Participants will walk at comfortable treadmill walking speed, without body-weight support other than handrail support. Comfortable treadmill walking speed will be determined at the beginning of each session in order to promote the quality and safety of walking as appraised by the physical therapist. The initial focus of conventional treadmill training will be on the quality and safety aspects of walking: therefore, therapists may give instructions regarding the walking pattern. After a safe walking pattern has been established, the focus will gradually shift towards walking faster and longer. Participants in the CT group will walk on the C-Mill treadmill (C-Mill, ForceLink, Culemborg, The Netherlands), but without projection of visual context on the belt’s surface.

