
**Figure 3 F3:**
[figure not shown]
**Examples of C-Mill gait adaptability exercises.** Participants practice visually guided stepping to a sequence of regular or irregular stepping targets (**A**), obstacle avoidance (**B**), speeding up and slowing down by maintaining position in a moving walking zone (**C**), and all of the above in a functional and interactive gait adaptability game (**D**).

Note that we predict that the intensity of training, in terms of number of performed steps, will be markedly higher for both treadmill training intervention groups (i.e., AT and CT) than for the UC control group. We will test this prediction by comparing the number of steps taken per session among groups. To this end, the number of steps taken during AT and CT training sessions will be registered using the treadmill’s step counter while an observer will count the number of steps taken during UC sessions in a random sample of participants. We expect a main effect of Group in a one-way ANOVA, with post-hoc independent *t*-tests revealing significantly fewer steps for the UC control group than for both AT and CT training groups, in the absence of a significant difference between the latter groups.

To assist the therapist in progressively scaling the AT and CT training sessions, the participant’s perceived rate of fear and difficulty during AT and CT sessions will be assessed at a scale from 0 (no fear/not difficult) to 10 (much fear/very difficult), as well as their perceived rate of exertion using the 15 grade Borg scale (range 6-20, [37]).

Finally, adherence will be reported and the content of all individual training sessions will be registered by the supervising physical therapist. Adverse events during training sessions will be reported as well, and after completing the last UC, CT or AT therapy session of the intervention period, participants will fill out a purpose-designed questionnaire to register perceived discomforts during and after training sessions. The participant’s experience with the therapy program will be evaluated with this questionnaire as well to be able to compare the feasibility of the interventions from a participant’s perspective.

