#### T3 (follow-up assessments)

All tests performed at T0 will be repeated after 12 months follow-up at T3 and participants will again be questioned about the use of assistive devices, tolerated walking distance, complications and physical therapy in the past 12 months. The HOOS will also be administered at T3. Furthermore, the occurrence of trips, slips and falls will be monitored monthly between T1 and T3 using a daily calendar diary for postal use [58]. When a fall occurs, the participant has to answer additional questions on the daily calendar diary regarding the circumstances of the fall and the injuries caused by the fall. If a calendar is not returned or information is incomplete, the participant will be reminded to return the calendar or the missing information will be obtained during a telephone conversation.

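### Neither complication question reaches the six training weeks, so a complication arising between sessions in that period has no stated collection point

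*Protocol article*

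**What the plan says.** **After training.** At T2 (retention assessments), participants are asked about "complications and physical therapy in the past four weeks". At T3 (follow-up assessments), they are asked about "complications and physical therapy in the past 12 months". The HOOS "will be administered to monitor symptoms and functional limitations related to the hip"; Table 1 marks it at T2 and T3. Trips, slips and falls are recorded in a diary that runs from T1 to T3.

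**At T1.** The T1 section lists physical and cognitive tests, fear of falling, perceived general health, living situation and assistive devices. It has no question on complications.

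**During training.** Therapy is planned as "five sessions per week) of therapy over a 6-week inpatient intervention period". The Intervention program section (text after Figure 3) says: "Adverse events during training sessions will be reported as well". The treating therapist records what each session contained. In all three arms, "after completing the last UC, CT or AT therapy session of the intervention period", participants complete a questionnaire on discomfort felt in and following sessions.

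**Analysis set.** Under Sample size and Data analyses, only participants with a minimum of four training weeks and both T0 and T1 are analysed, and those who do not adhere are replaced. Adverse events are summarised descriptively.

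**The concern.** The arms differ in treatment only during the six inpatient weeks, when CT and AT replace half of the conventional sessions with treadmill walking soon after a hip fracture. If one programme produced more complications than another, those weeks are where an excess would be expected to begin. The article's own complication question is nevertheless placed only where it looks back over the time after training.

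A reoperation, wound problem or other complication that arises on the ward between sessions is not an event in a session. Nor is it clearly what a questionnaire on discomfort from training would elicit.

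The analysis rule makes the gap worse. A complication serious enough to end participation before four weeks removes that person from the analysed set and brings in a replacement. A comparison of harms restricted to the per-protocol set would then leave out the participants most affected.

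**Working it through.** No figure computed in the plan bears on this point; the sample size calculation does not enter. The check is whether any stated collection point reaches a between-session complication in the training weeks.

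**Inputs (Protocol article)**
- Training: six weeks (Intervention program).
- T1: within one week after training ends (Study design).
- T2: four weeks after T1 (T2 section), given as one month in Study design.
- T3: 12 months after training ends (Study design).
- Look-backs: four weeks at T2, 12 months at T3.

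**Time axis.** Put the end of training at week 0, so training runs from week -6 to week 0. Window start = visit time minus look-back. Overlap with training = max(0, 0 - window start).

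| Visit | Timing assumed | Look-back window (weeks) | Overlap with training |
|---|---|---|---|
| T2 | T1 at week 0, gap 4 weeks | 0 to 4 | 0 |
| T2 | T1 at week 1, gap 4 weeks | 1 to 5 | 0 |
| T2 | T1 at week 0, gap one month (52/12 = 4.33 weeks) | 0.33 to 4.33 | 0 |
| T2 | T1 at week 1, gap one month | 1.33 to 5.33 | 0 |
| T3 | week 52 | 0 to 52 | 0 |

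Both questions miss all six training weeks under every reading of the visit timing. The T3 row takes the visit at its nominal date. A visit held some weeks early would nominally reach that many weeks into training, but only through recall over a year.

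**Other stated sources for weeks -6 to 0**

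| Source | Reaches a between-session complication? |
|---|---|
| Adverse-event reporting | Worded for events in sessions |
| Therapist's session record | Records session content |
| Closing questionnaire, all arms | Reaches discomfort following sessions; complications are not named |
| T1 assessment | No complication item listed |
| HOOS | First given at T2 |
| Fall diary | Starts at T1 |
| Medical files | Named as a source for T0 information; no stated use for later complications |

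**Interaction with the analysis set.** The 126 are participants who have met the four-week, T0 and T1 conditions, so the number randomised is 126 plus those replaced. That second number is not given. At 126/3 = 42 per arm, one uncollected complication is 1/42 = 2.4% of an arm. The article gives no complication rate, so the expected number missed cannot be computed.

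**The case against.** The strongest reply is that the training period is covered. Adverse events in sessions are reported, participants see a therapist five times a week, and all arms complete a closing questionnaire whose wording extends to the time following sessions. T1 also includes blinded mobility tests and a general-health scale on which a serious setback might show. The T2 and T3 look-backs are consistent with each other and complement this capture. Finally, a journal article condenses an ethics-approved protocol that may well contain general rules for serious events.

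Much of this stands, and it rules out several stronger readings that a reader might infer:
- *That hip symptoms are first asked about at T2, or that the six weeks go unobserved.* The closing questionnaire can pick up pain following sessions in every arm.
- *That only about 2% of the period is covered.* Session time is 30 x 40 min = 20 h of 42 x 24 = 1008 h. That is a share of clock time, not of events missed, and it ignores the questionnaire.
- *That there is a tenfold loading contrast in an unobserved window.* In the cited study of hip arthroplasty, patients "performed 1000-1500 steps during a conventional treadmill training session compared to 100-150 steps during an overground gait training session". CT and AT also have 15 conventional sessions and UC has 30. On the same borrowed figures the programme ratio is (15 x 1000 + 15 x 100)/(30 x 100) = 5.5, and the upper figures give 24,750/4,500 = 5.5. Steps are not hip load, and the treadmill steps are taken in the sessions where events are recorded.
- *That the HOOS belongs at T1.* It is listed as a secondary general-health outcome and has no T0 value. Its timing is a choice, not an error.

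The reply does not remove the narrower gap. The article sets out each visit and states the look-backs. It includes a complication question and places it only after training. That placement is stated, so the point does not rest on what a condensed article leaves out.

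**Conclusion.** The point holds in a limited form. The complication question covers none of the six training weeks, and the capture stated for those weeks does not name complications arising between sessions. The per-protocol rule and the replacement of non-adherers can then take the affected participants out of the analysed data.

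This is a cheap improvement to harm ascertainment. It is not a flaw in the efficacy design, and no two passages contradict each other. The size of the gap is six of six training weeks for the complication question; the number of events affected is unknown.

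The conclusion assumes that T3 takes place at its nominal date and that the full protocol has no general adverse-event procedure covering time between sessions. If it has one, the remaining task is to state it and to apply it to all randomised participants.

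**What to change.** 1. At T1, have the blinded assessor ask the complication question already used at T2 and T3, with a look-back to T0.
2. Check the answers against the medical files, already a data source at T0. For participants who stop early and do not attend T1, the files would be the main source. Someone other than the T1 assessor should do this check, so that the files do not reveal the allocation.
3. Report T0-T1 complications by allocated arm for all randomised participants, including those who stop early or are replaced, separately from T1-T3 complications.

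The cost is a few extra minutes at an existing visit and some record checking. No new instrument, visit or change to the efficacy analysis is needed.
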